#### 6.6 *Randomisation process & allocation concealment*

At the start of the study, the statistician responsible for randomisation will generate a group allocation sequence that will link participant IDs to either positive written disclosure (PWD), writing control activity (WC) or no writing task (NWC). Block randomisation will be used, and will be carried out by a statistician independent of the research team. The statistician will not have access to any of the personal information of the participants and will randomise using the participant identification numbers. Members of the research team will be blind to the size of the blocks. Randomisation will be carried out using a 1:1:1 ratio. The group allocation will be concealed from participants until after the baseline assessment is completed. The researcher responsible for carrying out the assessments will be blinded to the group allocation.

#### 6.7 *Procedure*

The study procedure is outlined in a CONSORT diagram (see below).

Once participants have been randomised to one of the three conditions: (1) PWD, (2) WC, or (3) NWC; they will be informed of the condition they have been allocated to and the relevant next steps. For participants in the NWC group they will be given an empty writing pack and will be asked to continue with their usual daily activities, and wait to receive the one month assessment pack. For those in the PWD or WC groups, they will receive their writing task and the relevant paperwork for this (see section 6.8 for details of the writing tasks).

There will be no further contact between the research team and the participants until the one month assessment – however participants will have the contact information of the research team in the event they need to make contact. At the one month assessment point, participants will be sent an assessment pack. Participants will be asked to complete some questionnaires and return them in a pre-post envelope within a week of receiving them. If participants were allocated to one of the writing conditions (PWD or WC) then we will also ask them to return their writing tasks. The writing tasks will be read by either CJ or MH to check for any signs of distress or risk. A copy of the writing tasks can be returned to the participants at a later date upon their request.

At both the 3 month and 6 month follow up time points, the procedure will follow that described above for the 1 month assessment. The assessments will be posted to participants to complete, and returned in the pre-post envelope. The only exception is that there will be no writing tasks to be returned. Participants will also have the option to complete the 1, 3 and 6 month assessments over the phone with a member of the research team whom is blind to their group allocation. Phone assessments will only be used where participants have been unable to complete the assessment themselves or return the booklet in the post. For all of the documents that need to be returned to the research team (i.e. assessment booklets and writing tasks), participants will be identified using a participant ID – no identifiable information will be recorded on these documents. For participants in the PWD group and the WC group, they will be offered an exit interview either in person or over the phone. The results of the study will be disseminated to all participants; the PPI consultants will help with this process.

[figure not shown]

**Figure One:** Study CONSORT

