### 6.5 Assessment process

| Assessment                   | Carried out by | What the assessment is for                                  | How is the assessment carried out            | At what stage is the assessment carried out |
|------------------------------|----------------|-------------------------------------------------------------|----------------------------------------------|---------------------------------------------|
| Baseline Assessment          | RF or RA       | Measure outcomes before randomisation                       | In person
Online or paper based           | After consent                               |
| 1 month assessment           | P              | Measure outcomes post intervention                          | Via post
Online or paper based            | 4 weeks post randomisation                  |
| 3 month follow up assessment | P              | Measure outcomes at short term follow up time point         | Via post
Online or paper based            | 12 weeks post randomisation                 |
| 6 month follow up assessment | P              | Measure outcomes at long term follow up time point          | Via post
Online or paper based            | 24 weeks post randomisation                 |
| Exit interview               | RF or RA       | Generate qualitative data on participants experience of PWD | In person or via telephone
Audio recorded |                                             |

RF= Research Fellow

RA= Research Assistant  
P= participant

The assessment will take place in either the participants own home or in a convenient NHS building (e.g. GP surgery or mental health building). Where assessments are carried out in the participant's home, the lone working policy will be followed (see section 9 – ethical considerations). The assessments at the 1, 3 and 6 month time points will not require any direct contact with the research team. The participants will be sent the assessment pack in the post with a covering letter. They will be asked to complete the questionnaires and return them in a pre-post envelope. Participants will also have the option to complete all assessments online (except for the exit interview).

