## 11 Schedule of events: Project timetable

| Week? | Event                                                                                                                                                                                     | Who?     |
|-------|-------------------------------------------------------------------------------------------------------------------------------------------------------------------------------------------|----------|
| 0     | Promote the study using the various recruitment methods                                                                                                                                   | RF
RA |
| 0     | Potential participant receives PIS via referrer                                                                                                                                           |          |
| 0     | Research team receives the referral                                                                                                                                                       |          |
| 1     | First contact is made with participant – the participant is given a copy of the PIS (if they have not received one already)                                                               | RF       |
| 1     | Initial meeting: participants ask questions, eligibility assessment, consent and baseline assessment                                                                                      | RF
RA |
| 2     | Randomisation to one of the three conditions (PWD, WC or NWC)                                                                                                                             | S        |
| 3     | Covering letter and writing task (if required) are sent to participants, depending on group allocation                                                                                    | RF       |
| 6     | 1 month assessment: participants are sent the assessment pack to complete, and those whom were allocated to the writing task conditions (WC or PWD) will be asked to return writing tasks | RF       |
| 14    | 3 month assessment: participants are sent the assessment pack to complete                                                                                                                 | RF       |

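### Writing tasks are asked for only with the 1-month pack, so the planned reading for distress or risk comes about 0 to 26 days after the third session; earlier return would be a minor, cheap safety improvement

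*Protocol*

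**What the plan says.** Section 11 gives the timetable. In week 3, "Covering letter and writing task (if required) are sent to participants, depending on group allocation". In week 6 the 1-month pack goes out, and "those whom were allocated to the writing task conditions (WC or PWD) will be asked to return writing tasks". Section 6.5 places this assessment at "4 weeks post randomisation".

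Section 6.7 describes the same sequence. After allocation, "There will be no further contact between the research team and the participants until the one month assessment", although participants may contact the team themselves. With the 1-month pack, "If participants were allocated to one of the writing conditions (PWD or WC) then we will also ask them to return their writing tasks". The questionnaires are due back within a week of receipt. Two members of the research team share the reading, and its stated purpose is "to check for any signs of distress or risk".

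The 3- and 6-month packs repeat the procedure with one difference: "The only exception is that there will be no writing tasks to be returned". The telephone route concerns the questionnaires: "Phone assessments will only be used where participants have been unable to complete the assessment themselves or return the booklet in the post".

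**The concern.** The sponsor chose to read the writing for distress or risk, and section 4.1 makes safety problems arising from the writing tasks a pilot question, item (g). The writing takes three days, but the workbook is not requested until three weeks after it was sent. For a participant who writes promptly, most of that time is waiting. If a worrying statement appeared only in the workbook, the risk procedure in section 9 could not start until the workbook had been posted and read. The delay comes from when the workbook is requested. The task itself does not need it, so it can be removed at little cost.

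**Working it through.** No power or sample-size formula applies. The check is calendar arithmetic.

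**Inputs**
- Randomisation in week 2, task sent in week 3, 1-month pack sent in week 6 (section 11).
- 1-month assessment 4 weeks after randomisation (section 6.5).
- Three sessions on consecutive days (sections 6.8.1 and 6.8.2).
- Questionnaires returned 0 to 7 days after receipt (section 6.7). I assume that the workbook is posted in the same window.
- 60 participants (section 7.3), allocated 1:1:1 (section 6.6).

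**Is the timetable consistent?** Yes. Week 6 − week 2 = 4 weeks. Likewise 14 − 2 = 12 and 26 − 2 = 24 weeks for the later assessments. All three match section 6.5.

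**Lag from third session to posting**

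Let day 0 be the day the task arrives. Outward post is assumed equal for the task and the pack, so it cancels. The pack then arrives on day (6 − 3) × 7 = 21, and the return is due by day 28. If writing starts on day s, the third session is on day s + 2, and

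lag = 21 − (s + 2) to 28 − (s + 2) days.

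| Writing starts | s | Third session | Lag (days) |
|---|---|---|---|
| On arrival | 0 | day 2 | 19 to 26 |
| One week later | 7 | day 9 | 12 to 19 |
| Two weeks later | 14 | day 16 | 5 to 12 |
| Third session on the day the pack arrives | 19 | day 21 | 0 to 7 |

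The overall range is about 0 to 26 days.

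**What early return saves.** If the workbook is posted on the day of the third session, the lag is 0. Return post and reading time are the same on both routes and cancel, so the saving equals the lag in the table.

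**Sensitivity of the on-arrival case**
- Section 11 gives weeks, not days. If each mailing can fall on any day of its week, the gap is 21 ± 6 = 15 to 27 days, and the lag is 15 − 2 = 13 to 27 − 2 + 7 = 32 days.
- If the task were handed over at randomisation instead of in week 3, the lag would be 28 − 2 = 26 to 26 + 7 = 33 days.
- An assumed 1 to 3 days of return post moves the workbook's arrival to 19 + 1 = 20 to 26 + 3 = 29 days after the third session.

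**Numbers affected.** 60 / 3 = 20 per arm, so about 20 in Positive Written Disclosure (PWD) and 20 in Writing Control (WC), 40 in all. A disclosure is least plausible in WC, where participants describe room images and are discouraged from giving feelings.

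**The case against.** The strongest reply is that nothing here is inconsistent. Sections 6.5, 6.7 and 11 agree, and late collection may be deliberate, since it suits a self-directed task and limits contact that could reveal allocation. The reading is also only one safeguard. Section 9 rates distress as unlikely and reports earlier caregiver writing trials without adverse outcomes. Support information is given at the start, the GP is told of participation, and participants hold the team's contact details. The 19 to 26 days apply only to those who write on arrival. The protocol sets no writing date, so the average saving is unknown. All of this stands. It limits the importance of the point but does not change when the reading happens.

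A reader might go further and infer that unreturned workbooks are never chased, because the 3- and 6-month packs collect none and the telephone route covers questionnaires only. The documents do not support this as a separate defect. The study materials in the appendices and the CONSORT figure are not shown, and a return prompt could sit in either. The absence of a reminder therefore applies to the visible text only.

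A reader might also take the planning margin of 20 − 12 = 8 per arm, or 16 across the two writing arms, as the number of workbooks that would go unread. That margin concerns completion of the baseline and 1-month assessments. It is a tolerance and not a forecast, and some of those participants may never have written. No workbook return rate is given, so no such number can be estimated.

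**Conclusion.** The point holds as a minor design improvement. Because workbooks are first requested in week 6, the protocol's own check for distress or risk is delayed by about 0 to 26 days after the third session. The lag is 19 to 26 days for someone who writes on arrival and close to nothing for late writers. Return post and reading time come on top.

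This rests on the section 11 weeks being exactly three weeks apart, equal outward post for both mailings, and the workbook being returned within the same week as the questionnaires. Nothing is assumed about when participants are told to write, because those instructions are not shown.

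A reader might infer that the safety plan fails. It does not: expected risk is low, other safeguards are in place, and the risk and adverse-event procedures in sections 9 and 10 do not depend on the workbook.

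**What to change.** Amend section 6.7 and the week 3 and week 6 rows of section 11 as follows.

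- Supply PWD and WC participants with a separate prepaid envelope addressed to the screeners, and ask them to post the workbook straight after the third session. Only the participant ID should appear on the workbook, as now.
- Keep the request in the 1-month pack as a back-up for outstanding workbooks. Word it as one conditional line in every arm's letter, for example: *If you were given a writing task and have not yet returned it, please post it in the envelope supplied with it.* The letter then stays identical across arms, as section 7.8 requires.

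The cost is about 40 prepaid envelopes and a wording change. The reading is already planned. The main downside is a separate mail stream that shows membership of a writing arm, so it must be kept away from blinded assessors and from the data-entry assistant. Including WC takes about 20 of the 40 envelopes but means that an envelope does not distinguish PWD from WC. Postal screening still would not be real-time, and a workbook that is never posted would remain unread.

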## 6.8 Therapy protocols

### 6.8.1 Positive Written Disclosure (PWD)

The intervention being investigated in the present study is Positive Written Disclosure (PWD). PWD is a self-directed and time-limited therapy. The intervention is based on the wealth of literature on the effects of Written Emotional Disclosure (WED) (Frattaroli, 2006); however in recent years the literature has changes from focussing on negative emotional writing, to writing about positive

emotions (Ashley, O'Connor & Jones, 2011). PWD will require participants to take 20 minutes out of their day, for three consecutive days to write continuously about a positive memory or experience.

Participants will be encouraged to describe this positive event in a lot of detail, focussing on the subjective experience. Participants will be provided with a workbook and a set of writing instructions within which to complete the PWD writing tasks. The PWD workbook and instructions are based on the materials used in similar research studies that were found to be acceptable to participants (Ashley, O'Connor & Jones, 2011; Jones et al., 2015). It is hoped that taking some time to focus on this positive experience or memory will help to improve the wellbeing of our participants (older adult caregivers of people experiencing psychosis).

### **6.8.2 Writing Control (WC) task**

The writing control group within this study will be asked to complete a non-emotive writing task. The participants allocated to this group will also receive a workbook and a set of writing instructions. The writing task will require participants to look at images of different rooms within a house and describe them as accurately and in as much detail as possible. The images were selected to be neutral (not provoke any strong positive or negative feelings) and also rich in detail – so that participants have enough to write about. The final images were selected by our lived experience advisory panel. Participants will be asked to write about these images continuously for 20 minutes over three consecutive days. The instructions for the writing task encourage participants to not give their feelings or opinions towards the images, and instead stick to the facts.

### **6.8.3 Non-Writing Control (NWC) task**

The non-writing control group will not be asked to complete any writing tasks over the course of the study – they will receive no intervention. Participants in this group will be encouraged to carry on with their usual activities, as if they were not part of the research study. So as to maintain researcher blinding, this group will receive a writing pack that is empty. The inclusion of this control group was one outcome of the PPI consultation. Caregivers said that being able to take 20 minutes out of their day to complete a writing task, irrespective of the type of writing, could have some therapeutic effects: caregivers are often preoccupied with the needs of their care recipient, so taking 20 minutes for themselves could provide a brief respite. The non-writing control task will help us to identify whether it is the act of writing or the content of the writing that has beneficial effects.

## **6.9 Primary & Secondary Outcome Measures**

As participants will be required to complete some of the assessments independently (without contact from a member of the research team) all of the measures included are self-report. If participants do have any questions when completing the measures they will be encouraged to contact a member of the research team to discuss this. The measures included in this study have been chosen to capture all of the hypothesised changes that may occur as a result of PWD. The measures

included hope to capture the improvement of positive aspects of the participant's wellbeing, and reductions of the negative aspects.

### 6.9.1 Co-Primary Outcomes:

The co-primary outcome for this pilot trial will be the Positive and Negative Affect Scale (PANAS) (Watson et al., 1988).

- This measure has two subscales: positive affect, and negative affect
- Each scale is comprised of 20 items
- This measure was chosen because we hypothesise that PWD will increase positive moods and reduce negative ones
- This measure has strong internal consistency (Cronbach's  $\alpha > .84$ )

### 6.9.2 Secondary Outcomes:

Depression Anxiety and Stress Scale (DASS 21) (Lovibond, 1983).

- This measure has three subscales: anxiety, stress and depression
- Each scale is comprised of 7 items
- This measure will allow us to observe any changes in clinical and sub-clinical levels of anxiety and depression, as well as stress
- This measure has strong internal consistency (Cronbach's  $\alpha = .88$ ) (Henry & Crawford, 2005)

General Self-Efficacy Scale (GSES) (Schwarzer & Jerusalem, 1995).

- This measure has one subscale: self-efficacy
- The questionnaire is comprised of 10 items
- This measure will allow us to observe any changes in participant's beliefs related to their self-efficacy
- This measure has strong internal consistency (Cronbach's  $\alpha > .86$ ) (Luszczynska et al., 2005)

Caregiver Wellbeing and Support Scale (CWSv2) (Quirk et al., 2009).

- This measure has one subscale: wellbeing
- Each scale is comprised of 32 items
- This measure will allow us to observe any changes carer-related aspects of wellbeing
- This measure has strong internal consistency (Cronbach's  $\alpha = .96$ )

Toronto Alexithymia Scale (TAS 20) (Bagby et al., 1994)

- This measure has three subscales: difficulty describing feelings, difficulty identifying feelings, and externally-orientated thinking
- These scales are made up of 5, 7 and 8 items respectively
- This measure will allow us to identify participants who have difficulty identifying and describing their emotions – this has been previously identified as a moderator of PWD treatment outcomes
- This measure has strong internal consistency (Cronbach's  $\alpha > .70$ ) (Parker et al., 2003)

EQ-5D health questionnaire (Taylor et al., 1992).

- This measure has one subscale: general health

- This questionnaire is made up of 6 items
- This measure will allow us to observe any changes in participants general health, including both physical and mental health
- This measure has strong internal consistency (Cronbach's  $\alpha = .85$ ) (Tran et al., 2012)

Leisure Time Satisfaction Measure (LTS) (Stevens et al., 2010).

- This measure has one subscale: satisfaction with leisure time
- This questionnaire is made up of 6 items
- This measure will allow us to observe any changes in participants perceived satisfaction with the quality of their leisure time
- This measure has strong internal consistency (Cronbach's  $\alpha = .94$ ) (Martinez-Rodriguez et al., 2016)

## 7 Data Management & Analysis

### 7.1 Summary of the Types of Data

This research study will collect both quantitative and qualitative data. Quantitative data will be collected in the form assessment made up of validated questionnaires. The quantitative data will be collected at four time points: baseline, and 1, 3 and 6 months post randomisation. The questionnaires used have been selected to capture any changes in the hypothesised mechanisms and/or treatment outcomes of PWD. The quantitative data can be completed either using paper-based booklets or online using Bristol Online Survey.

Qualitative data will also be collected in the form of 1:1 interview based on the Change Interview (Elliot et al., 2001). The interview discussion guide was adapted in line with the feedback from the lived experience advisory panel. These interviews will be conducted after all quantitative data has been collected. Exit interviews will only be conducted with those allocated to one of the writing conditions. The interviews will ask participants to talk about their experience of changes during the tasks, if any, their attributions for any changes and their views on the helpful and unhelpful aspects of the intervention.

